### Assessment of balance

Balance is assessed using the Sensory Organization Test (SOT) performed using a dynamic posturographic EquiTest® System (NeuroCom® International, Inc., Clackamas, OR, USA). The SOT measures the participants’ ability to effectively use visual, vestibular, and somatosensory information to maintain balance. Before testing, participants are strapped into a harness attached to a support beam and positioned on the fixed platform in the proper foot alignment. There are six different conditions for the SOT: (1) eyes open with a fixed floor; (2) eyes closed with a fixed floor; (3) eyes open, fixed surroundings, and floor sways; (4) eyes closed, fixed surroundings and floor sways; (5) eyes open, surroundings sway and fixed floor; (6) eyes open, both surroundings and floor sway. Participants are asked to stand as still and stable as possible during each test, and each testing condition is measured three times. The support surface that participants stand on and the visual surroundings move or sway in response to a participants’ sway during the test. The SOT provides a composite equilibrium score that reflects the participant's sway in both anterior and posterior directions. High scores indicate greater stability and less sway.

The NeuroCom Balance Manager Software (NeuroCom® International, Inc., Clackamas, OR, Unites States) is used to process the raw data and calculate the balance outcome variable, the SOT composite equilibrium score. The SOT equilibrium score has demonstrated moderate to excellent test-retest reliability in healthy older adults and individuals with Parkinson’s disease [19–21]. As shown in Table 4, the study protocol for assessing the SOT composite equilibrium scores demonstrated moderate test-retest reliability (*r* > 0.87; ICC > 0.67) [35].

### Assessment of lower extremity muscle strength

Isometric strength of hip, knee, and ankle flexor and extensor muscles is assessed using an isokinetic dynamometer, Biodex BX Advantage (Biodex Medical Systems, Shirley, NY, USA), and the computer software program version 3.29 and 3.30. The test protocols have been established based on the Biodex BX Advantage manual and recommendations from other studies [22–25]. The dominant and non-dominant legs are tested. Before each test, participants will become familiar with the procedures by performing 2–3 contractions as warm-ups. During the test, participants are guided with standardized instructions during the test to encourage sub-maximal muscle performance. Participants are stabilized in the chair with shoulder and abdominal straps. The anatomical axis of rotation is aligned to the dynamometer axis using visual inspection and manual palpation. The isometric tests include three sets of sub-maximal muscle contractions, each set lasting 5 s separated by 10 s rest intervals. The isometric strength of the hip muscles is assessed with subjects in a supine position with the hip joint positioned at 45° of flexion [22]. For assessment of the knee muscles, subjects are positioned in sited position with the knee positioned at 60° of flexion [36, 37]. To evaluate the ankle muscles, subjects are positioned in a sited position with the ankle joint positioned in a neutral position (0°) [38]. Participants performed three sets of isometric contractions for extensor and flexor muscles of the hip, knee, and ankle joints. The reliability of muscle strength values measured using isokinetic dynamometers is excellent [39, 40]. It has shown good to excellent reliability in healthy older adults and patients with hereditary motor sensory neuropathy [25, 41]. As shown in Table 3, the lower extremity muscle strength measures used in this study demonstrated good to excellent test-retest reliability (*r* > 0.7; ICC > 0.80) [35].

The Biodex Advantage BX 4. X Software is used to calculate the peak torque [Newton-meters, Nm] (i.e., highest force output during each sub-maximal muscle isometric contraction) and the average peak torque (i.e., average force output of a given set). The average peak torque (Newton-meters, Nm) obtained in each series is used for data analysis.

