### Outcomes

The primary outcome is to assess the effects of exercise on gait, balance, and lower extremity muscle strength in 312 women randomized to either a 16-week home-based gait/balance intervention or an attention control educational cancer survivorship condition. The gait assessment includes spatiotemporal metrics (cadence, speed, foot strike angle, stance percent, stride length, and swing percent) and lower extremity joint kinematics (hip, knee, and ankle joint angles). The APDM Opal (Mobility lab v1, APDM, Inc., Portland, OR) inertial measurement units (IMU) system assesses gait. The APDM IMUs are wireless sensors for measuring motion that allows clinicians to perform gait assessments quickly and straightforwardly [17, 18]. Balance is assessed using the Sensory Organization Test (SOT) performed using a NeuroCom Balance Master (NeuroCom International Inc, Clackamas, OR) and the EquitTest System (v8.0). The SOT measures the participants’ ability to effectively use visual, vestibular, and somatosensory information to maintain balance. The SOT equilibrium score has demonstrated moderate to excellent test-retest reliability in healthy older adults and individuals with Parkinson’s disease [19–21]. Isometric strength of hip, knee, and ankle flexor and extensor muscles is assessed using an isokinetic dynamometer, Biodex BX Advantage (Biodex Medical Systems, Shirley, NY, USA), and the computer software program version 3.29 and 3.30 [22–25]. We also assess neuropathy symptoms using the FACT-Taxane Additional Concerns Subscale and nerve conduction velocity of the sural and peroneal nerve action potentials [26, 27]. Different outcomes will be analyzed separately. Multiple comparison methods such as the Bonferroni-Holm Method will be applied to control family-wise error rates.

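### The strength test is described three times as sub-maximal with no target or scaling, yet its raw torque is analysed as muscle strength, a primary domain; the two must be reconciled

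*Protocol article*

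**What the plan says.** Under Outcomes, the protocol article states: "The primary outcome is to assess the effects of exercise on gait, balance, and lower extremity muscle strength". The construct is named there too: "Isometric strength of hip, knee, and ankle flexor and extensor muscles is assessed using an isokinetic dynamometer".

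The section on assessment of lower extremity muscle strength then describes the effort required, at three separate steps:

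- the instruction: "participants are guided with standardized instructions during the test to encourage sub-maximal muscle performance"
- the task: "The isometric tests include three sets of sub-maximal muscle contractions, each set lasting 5 s separated by 10 s rest intervals"
- the definition of peak torque: "highest force output during each sub-maximal muscle isometric contraction"

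The analysed variable is absolute torque: "The average peak torque (Newton-meters, Nm) obtained in each series is used for data analysis". The support offered is repeatability: "the lower extremity muscle strength measures used in this study demonstrated good to excellent test-retest reliability". The values stand in Table 4, with ICCs from 0.85 to 0.97.

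The Data analysis section compares the change in each metric from baseline to 16 weeks between the arms. The section on allocation and blinding lists the PI, the data collectors and the principal statistician as blinded. Participants are not listed.

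**The concern.** Strength is usually understood as the most force that a person can produce. If participants are asked for less than that, and nothing fixes how much less, the recorded torque depends on capacity and also on the fraction of it that the participant uses. The two cannot be separated afterwards.

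This can distort the comparison in two directions:

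- **Dilution.** A participant who has become stronger need not use the gain in a sub-maximal contraction. Variation in effort between people also adds noise.
- **False gain.** One arm does 16 weeks of resistance exercise, and the other agrees not to start a new exercise program. Participants therefore know what they received. If trained participants push harder at week 16, that shift goes straight into the between-arm difference in change.

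What is at stake is the interpretation of a whole primary domain. It cannot be recovered once the data are collected.

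**Working it through.** **1. The statements side by side.** The protocol gives no figure to reproduce here, so the first check is of wording. The instruction, the task and the outcome definition all say sub-maximal. No section of the article asks for maximal effort in this test, gives a target fraction of maximum, or expresses torque relative to a reference contraction. By contrast, the balance section asks participants to stand as steadily as they can, which is a request for best performance. The strength section is therefore consistent about effort, but inconsistent with the name and the use of the outcome.

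**2. What Table 4 shows.** Five of the six strength ICCs are 0.94 or above; hip extension is 0.85. This shows that readings repeat. It does not show that they reflect capacity, or that effort would stay equal between a trained and an untrained arm.

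**3. Effect of a shift in effort (illustration).** Write torque = capacity × effort fraction. Assume effort of 70–80% of maximum and a shift of 5 percentage points, neither of which is in the documents:

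- 5/80 = 6.3%
- 5/70 = 7.1%

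Torque changes by about 6–7% with no change in strength.

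**4. Scale of a false gain (illustration).** The documents give no SD for torque, so assume a coefficient of variation (CV) of 25–35%. The spurious standardized difference is d = relative effort difference / CV. The chance of a significant result in a plain two-sample comparison, at two-sided 0.05 and before any Holm adjustment, is about Φ(d√(n/2) − 1.96). Here n = 312/2 = 156 per arm, or 312 × 0.8/2 ≈ 125 with the stated 20% attrition.

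| Relative effort difference | d (CV 35% to 25%) | n = 156 per arm | n = 125 per arm |
|---|---|---|---|
| 5% | 0.14 to 0.20 | 24% to 42% | 20% to 35% |
| 10% | 0.29 to 0.40 | 71% to 94% | 62% to 89% |

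The nominal rate is 5%. The 10% row lies around the protocol's own minimum detectable effect of 0.30.

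**5. Scale of dilution (illustration).** If effort varies between people independently of capacity, with CV e, and capacity has CV c, a true d of 0.30 shrinks to 0.30 × c/√(c² + e²). With c = 0.30 and e = 0.20 (both assumed), this is 0.30 × 0.30/√(0.09 + 0.04) = 0.25. In the same plain comparison at 156 per arm, power falls from 0.755 to 0.597. These powers are for scale only and are not a check of the protocol's simulated 0.81.

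**6. How much of the primary family is exposed.** Six muscle groups are tested (flexors and extensors at hip, knee and ankle), on both legs. That makes 6 × 2 = 12 metrics at most, if the legs are analysed separately. The article does not say that they are, and Table 4 lists six.

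**The case against.** The strongest reply is that this is a misused term. An author who uses a word wrongly may do so throughout a section, so three uses do not prove that sub-maximal testing was intended. The same section speaks of strength, peak torque, standardized instructions, warm-up contractions and protocols based on the device manual. ICCs of this size would be surprising if effort were loosely chosen. This stands as a live explanation, and it is why the first step must be to find out what participants were told. It does not settle the matter, because nothing in the article says that effort was maximal.

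A second reply is that an article need not print the test script or a target level. That is right, and the absence of a target is not a finding in itself. The point rests on what the article does state about effort.

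A third reply is that data collectors are blinded and the control arm receives attention contacts. Both mitigate the bias. Neither governs how hard a participant who knows her allocation pushes. Equally, such expectation effects also reach maximal voluntary testing, so a maximal script reduces this bias but does not remove it.

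A reader might go further and infer that the recorded torque is not strength at all. The documents do not support that: sub-maximal torque still partly reflects capacity, and the supportable claim is that capacity and effort are mixed.

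**Conclusion.** The point holds as an inconsistency with consequences. The text describes a sub-maximal test and analyses its raw torque as strength, in one of three primary domains. If the text was followed, a between-arm difference in torque cannot be attributed to strength alone, and a null result cannot be read as no gain in strength. If testing was in fact maximal, only the wording is wrong and no data are affected.

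The direction and size of any bias are unknown. The 5-point effort shift, the 70–80% effort level and all CVs are assumptions. They show only that modest shifts in effort would matter beside a planned detectable effect of 0.30.

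Two further inferences should be avoided. The count of 12 strength outcomes is an upper limit that depends on how the legs are handled. And the 33 participants under Trial status (33/312 = 10.6%) are those recruited when the article was written, with recruitment planned to July 2024. That number is a minimum for those tested under this wording, not a ceiling.

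**What to change.** 1. **Confirm the instruction.** Establish from the laboratory procedure and the assessors which effort was asked for, and reconcile the terms strength and peak torque with sub-maximal.
2. **If testing was maximal,** correct the three statements. The cost is a text change.
3. **If testing was sub-maximal,** choose one of two courses:
   - Amend the script to maximal voluntary isometric contraction with standardized encouragement, for participants whose baseline follows the amendment. Keep the baseline instruction at week 16 for everyone already tested, so that it is constant within each person. Report the strength results with and without those participants.
   - Otherwise, report the outcome as sub-maximal torque and draw no primary conclusion about strength from it.

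The script change uses the same device, visit and warm-ups. Its main cost is that two instructions are mixed within one outcome. At least 33 participants fall under the present wording, and more will by the time of an amendment, so the analysis without them loses precision. Allocation is randomized, so both instructions should occur in both arms; their split by arm should be reported.

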### Assessment of neuropathy symptoms

Patient-reported symptoms are assessed using the Functional Assessment of Cancer Therapy-Taxane (FACT-Taxane) Additional Concerns subscale. FACT-Taxane contains five domains comprised of questions about physical well-being, social well-being, emotional well-being, functional well-being, and additional concerns subscale. The FACT-Taxane Additional Concerns subscale comprises sixteen questions that address symptoms specific to neuropathy, with scores for each question ranging from 0 (not at all) to 4 (very much). Higher scores indicate more neuropathy symptoms [26].

### Nerve conduction velocity

A combination of a clinician-based test and a patient-reported questionnaire has been suggested as a proper assessment tool to evaluate taxane-induced neuropathy [27]. Sensory and motor nerve conduction studies are conducted on the sural and peroneal nerves. The nerve conduction velocities and amplitudes of each nerve are collected for comparison over time [27].

### Plans to promote participant retention and complete follow-up

Follow-up telephone calls to study participants in the intervention group are made weekly for the first month, then bi-monthly. Participants in the attention control group receive monthly phone calls as social contact and serve as a reminder for data collection appointments and review educational brochure topics. In addition, four newsletters are sent monthly to all study participants. Newsletters contain study recruitment updates and general health tips that do not influence study outcomes.

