#### Attention control protocol

Participants in the attention control group receive a journal to record their clinic appointments and standardized breast cancer survivorship education based upon information from the American Cancer Society. At each data collection encounter, the intervention research assistant discusses the information in each pamphlet, allowing time for questions related to the material. In addition, participants in the attention control group receive telephone calls every other week which entail a social visit and reminder of data collection/attention intervention appointments to equalize contact further.

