### Strategies to improve adherence to interventions

The following strategies are used to increase adherence to the exercise program. (1) The exercise program is designed to be done at home, moving away from supervised sessions, to be more in context with natural living conditions; (2) the exercise program components are designed to be completed either in one session or split sessions; (3) the exercise program was designed to minimize injuries/soreness by beginning light-moderate and increasing over time; (4) the exercise program contains a self-monitoring Exercise Diary in REDCap and weekly telephone follow-ups to provide coaching regarding exercise-related issues and encourage completion of the Exercise Diary throughout the study period.

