### Participant timeline

Table 3 shows the participant timeline.

**Table 3 Tab3:** Participant timeline

Recruitment Screening Study information	
**Baseline visit:** Informed consent Baseline assessment of gait, balance, muscle strength Neuropathy symptoms patient-reported questionnaire Nerve conduction velocity assessment Randomization	
**Home-Based Physical Activity Intervention group**	**Educational attention control group**
Week 1–week 4	Week 1–week 16
Gait/balance exercise and resistance exercises 3 days per week Exercise diary Follow-up phone call weekly	Standardized breast cancer survivorship education from American Cancer Society Follow-up phone call bi-weekly
Week 5–week 16 Gait/balance exercise and resistance exercises 3 days per week Exercise diary Follow-up phone call bi-weekly	
**End of treatment visit:** Baseline assessment of gait, balance, muscle strength Neuropathy symptoms patient-reported questionnaire Nerve conduction velocity assessment	**End of treatment visit:** Baseline assessment of gait, balance, muscle strength Neuropathy symptoms patient-reported questionnaire Nerve conduction velocity assessment

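### Control-arm phone calls are stated both as every other week and as monthly, and each place that sets out both arms gives the intervention arm more calls, so the stated aim of equalizing contact is not met

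*Protocol article*

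**What the plan says.** **Control arm.** Under Attention control protocol, control participants "receive telephone calls every other week which entail a social visit and reminder of data collection/attention intervention appointments to equalize contact further". Table 3 (Participant timeline) agrees, listing "Follow-up phone call bi-weekly" for weeks 1 to 16. Under Plans to promote participant retention and complete follow-up, the text reads "Participants in the attention control group receive monthly phone calls as social contact"; the same sentence adds that these calls serve as appointment reminders and go over the brochure topics.

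**Intervention arm.** Strategies to improve adherence to interventions lists "weekly telephone follow-ups to provide coaching regarding exercise-related issues and encourage completion of the Exercise Diary throughout the study period". Table 3 has weekly calls in weeks 1-4 and then "Follow-up phone call bi-weekly" in weeks 5-16. The retention section says "Follow-up telephone calls to study participants in the intervention group are made weekly for the first month, then bi-monthly". The Intervention protocol section mentions calls to help with barriers to exercise but gives no frequency.

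**Aim.** Background and rationale and Outcomes both describe the trial as assessing the effects of exercise against an attention control condition.

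**The concern.** An attention control is there so that staff contact does not differ between arms along with the treatment under test. The protocol says that this is what the control calls are for. If the schedule is contradictory, staff may apply either version. If every schedule covering both arms is unequal, contact differs by arm even when the protocol is followed exactly.

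The outcomes are not equally exposed:

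- The FACT-Taxane subscale is self-reported by participants who know whether they are exercising.
- Strength is measured from sub-maximal contractions performed to standardized encouragement, so it depends on effort. A blinded data collector does not remove an effect of contact on the participant's own effort.
- The calls are also presented as a retention measure, in a trial planned around 20% attrition. Unequal calls could therefore bear on who returns at week 16.

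**Working it through.** The protocol states no call totals, so there is no figure to reproduce. The check counts scheduled calls under each stated frequency.

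**Inputs and assumptions**

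- Intervention period: 16 weeks.
- Table 3's bi-weekly is read as every two weeks. The Attention control protocol says every other week for the same control calls, and after a weekly phase only this reading is a taper.
- The first month is taken as weeks 1-4, leaving 12 weeks. A calendar month is 52/12 = 4.33 weeks.

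**Control arm**

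- Attention control protocol: 16 / 2 = 8 calls.
- Table 3: 16 / 2 = 8 calls.
- Retention section, monthly: 16 / 4.33 = 3.7, about 4 calls.

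**Intervention arm**

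- Adherence section, weekly with no taper stated: 16 / 1 = 16 calls.
- Table 3: 4 + 12 / 2 = 10 calls.
- Retention section, 'bi-monthly' as twice a month: 4 + 2 × (12 / 4.33) = 4 + 5.5 = 9.5, about 10 calls.
- Retention section, 'bi-monthly' as every two months: 4 + 12 / (2 × 4.33) = 4 + 1.4 = 5.4, about 5 calls.

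**Arms compared within one place**

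| Source | Intervention | Control | Excess in intervention arm |
|---|---|---|---|
| Table 3, weeks 1-4 | 4 | 2 | 2 |
| Table 3, weeks 5-16 | 6 | 6 | 0 |
| Table 3, total | 10 | 8 | 2 |
| Retention section, twice a month | about 10 | about 4 | about 6 |
| Retention section, every two months | about 5 | about 4 | 5.4 - 3.7 = 1.7 |

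Two results follow. The control arm has 8 or about 4 calls, a twofold difference that no choice of reading removes. And neither place that sets out both arms gives equal call totals.

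**The case against.** The strongest case on the other side has four parts.

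1. **Most of the intervention-arm conflict may be loose wording.** 'Bi-monthly' can mean twice a month, and the retention section then agrees with Table 3 at about 10 calls. The adherence section may be shorthand for the tapered schedule, since its closing words about the study period can attach to completing the diary. This stands. The intervention-arm inconsistency is softer than the control-arm one.
2. **The gap may be small.** If Table 3 governs, it is two calls, both in the first four weeks, with identical frequency afterwards. This stands, but the protocol does not say that Table 3 governs.
3. **Exact equality was not promised, and coaching may belong to the intervention.** Equalizing contact further is weaker than matching it call for call, and calls about barriers to exercise could be a component of the package. That is a defensible design, but the comparison is then exercise plus coaching, which the stated aim does not say.
4. **The main outcomes are instrumented.** Gait, balance and strength are measured by device with a blinded data collector, and all participants receive the same newsletters. This limits the concern for those outcomes, though not for self-report, effort or retention.

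A reader might also infer three stronger points that the documents do not support:

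- **That control participants get no education between visits.** It is true that "At each data collection encounter, the intervention research assistant discusses the information in each pamphlet", and outcomes are collected only at baseline and week 16. But the retention section has the control calls cover brochure topics, and Table 3 lists the education across weeks 1-16.
- **That education at the assessment visit breaks the blind.** The discussion is assigned to an intervention research assistant, the data collector is described separately as blinded, and nothing places the two together.
- **That the imbalance could be fourfold, or could favour controls.** Either result needs one section's intervention schedule set against another section's control schedule. No single place describes such a trial.

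**Conclusion.** The point holds in a limited form. The contradiction in the control-arm schedule is plain: about 8 calls or about 4. On either schedule that covers both arms, the intervention arm receives more calls: two more under Table 3, and about six more (or between one and two more) under the retention section, depending on what 'bi-monthly' means. The stated aim of equalizing contact is therefore not met as written.

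The counts assume one call per stated interval and bi-weekly read as every two weeks. The documents give no basis for saying how far a few calls would move any outcome, so this is a confound of unknown, possibly small, effect. They do not show that a treatment difference would be uninterpretable or that dropout will differ by arm. Confidence is high for the control-arm contradiction and lower for the intervention-arm variants. It should be corrected, and it does not threaten the design as a whole.

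**What to change.** - Reconcile the Attention control protocol, the adherence strategies section, Table 3 and the retention section to one call schedule for each arm. The Intervention protocol section states no frequency and needs no correction.
- Replace 'bi-monthly' with an explicit interval in weeks.
- Give both arms the same number and timing of calls. If Table 3 is kept as the base, for example, two further control calls in weeks 1-4 would make it 10 against 10.
- If the coaching calls are meant as part of the intervention, say so, and describe the contrast in the aim and outcomes as exercise plus coaching.

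The cost is protocol wording and, on the Table 3 example, two short calls per control participant by staff who already phone participants. At the protocol date, 33 of the planned 312 women had been recruited, so a correction then would have covered most of the sample.
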